### Summary of Past Work by the Research Team

Our research team has conducted four studies that lay the foundation for the intervention described below. In our past work, we found that physicians have overly ambitious communication goals, planning to discuss over 30 pieces of information during a discharge consultation (Study 1), and that these high goals are shared by patients (Study 2). However, in real interactions, time spent with discharge communication is much more limited than the time allotted in Study 2, and the content and quality of information provision does not match the high goals of experts and patients (Study 3). Finally, experimental work using simulated discharge communication situations suggests that information structuring can be an effective tool to improve patients’ recall of information (Study 4). All in all, these results suggest that there is need for improving discharge communication and that information structuring may be a tool to both standardize communication and improve patients’ recall of information and, consequently, adherence to health recommendations. In what follows, we present our plan to test an intervention that provides training on information structuring to physicians and assesses the associated outcomes in patients’ information recall, satisfaction, and adherence to recommendations.

|  | |
| --- | --- |
| A | B |
| [figure not shown] |  |
|  | |

Figure 2. **A** Number of items recalled by participants that viewed either the structured or unstructured video by group (third-year medical, first-year medical, first-year psychology students). **B** Participants’ ratings of physician’s comprehensibleness, information structuring, and willingness to recommend the physician to family and friends as a function of whether they viewed the structured, InFARCt-based video (black icons) or the unstructured video (grey icons).

## Investigational Product (treatment, device) and Indication

**Physician Training**

Physicians will be recruited to participate in the study, which will serve as a complement to physicians’ regular emergency department training. The two programs will follow the same structure, with physicians receiving the same intensity of teaching. Both programs will consist of one four-hour session of training with an experienced communication expert ([name] [name]). Also, both training programs will consist of theory and practice components as well as a test session to assess the actual use of communication skills. The information-structuring program will include a review of scientific evidence on the superiority of structured over non-structured communication as well as hands-on practical exercises in dyads to train structured communication skills. Specifically, participants will be introduced to the InFARcT-scheme and trained to use it to structure their communication. The emotion skills training program will follow a similar structure but will focus on the NURSE communication model.^28^ The NURSE model encourages caretakers to engage in **n**aming, **u**nderstanding, **r**especting, **s**upporting, and **e**xploring patients’ emotional reactions with the goal of reducing anxiety and increasing compliance. In addition, physicians in both conditions will receive a one-hour booster session two weeks after the initial training involving a discussion of patient examples to whom they had applied the newly acquired skills. The rationale for the use of a booster session is to ensure that communication goals are maintained as a high priority and that physicians have a chance to receive additional feedback early in their training.

## Preclinical Evidence

See 3.1

## Clinical Evidence to Date

See 3.1

## Dose Rationale / Medical Device: Rationale for the intended purpose in study (pre-market MD)

NA

## Explanation for choice of comparator (or placebo)

We will compare the effects of information structuring to a control training condition in which physicians will receive emotion skills training by the same experts. A systematic review of emotion skills training suggests that these have the potential to improve physician–patient interactions.^23^ However, emotion skills interventions are not geared to changing the structure of the information provided and thus represent a powerful control for our study. In particular, it will ensure that any effects in information recall and patient satisfaction can be attributed to the information structuring program rather than a general emphasis on communication training and patient satisfaction during physician training.

## Risks / Benefits

We consider the risk of the study being low. There won’t be a direct benefit for the participants considering monetary compensation but previous studies found an effect of physician’s training in students. Therefore there might be a chance, that patients will benefit from physician’s training in both groups (information structuring & emotion skills training) in this intervention study as well..

## Justification of choice of study population

Chest pain accounts for up to 10% of all patient encounters in emergency departments.^8^ However, many patients with chest pain presenting to an emergency department are discharged within hours, once serious conditions, such as myocardial infarction, have been excluded and when further evaluation of low-to-intermediate risk patients is not possible in the context of the emergency department.^9^ Additionally, after the emergency department work-up and discharge, many patients have repeated episodes of chest pain, often associated with anxiety and uncertainty about diagnosis and outcome.^10^ Therefore the reduction of anxiety and uncertainty about the diagnosis is an important issue for this patients. We included patients with abdominal pain because the same applies to patients with abdominal pain.

Signs and symptoms showing that the participant is unwilling to participate in the study will result in the participant being excluded from participation. We guarantee that a physician not participating in the study, safeguards participant interest and insures proper medical care.

# STUDY OBJECTIVES

## Overall Objective

The goal of the proposed study is to assess the potential of information structuring for improving discharge communication. Specifically, we aim to examine the advantages of an information-structuring skills training for physicians (compared to an emotion skills training) on discharge communication and associated patient outcomes.

## Primary Objective

The primary outcome of the study will be patients’ recall of information as a function of physicians’ training.

## Secondary Objectives

The secondary outcomes will be higher patient satisfaction,^4^ better adherence to medication,^4,5^ more adequate disease management,^6^ and reduced anxiety.

## Safety Objectives

The study aims to improve discharge communication and associated patient outcomes.

# STUDY OUTCOMES

## Primary Outcome

Participants’ recall of discharge information will be assessed after the discharge communication and 1 week later. We measure this primary outcome to check whether the intervention was successful or not. We measure the recall 1 week and 30 days later to check the long-term effect of the intervention.

## Secondary Outcomes

Satisfaction with the discharge communication event and the physician directly after the discharge event. The rationale for including this measure is that it is a potential moderator of participants’ recall of discharge information and thus should be included in the statistical analysis.

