Our analyses had two aims. First, our main goal was to test the effects of information structuring on information recall and possible interactions with prior expertise. Second, we tested for superiority of information structuring relative to unstructured communication on perceived comprehensibleness and satisfaction. In total, participants recalled 9 of 28 items presented by the emergency physician (range: 0-23 items). An analysis of variance with condition (structured vs. unstructured), group (third-year medical, first-year medical, first-year psychology), and their interaction as factors, revealed a main effect of structure, *F*(1,228)=26.6, *p* < .001, as well as a expertise, F(2,228)=7.0, *p* = .009. As can be seen in Figure 2B, those participants that viewed the video structured according to the InFARCt categories listed 1 to 3 additional pieces of information relative to those who viewed the unstructured video. Also, third-year medical students did considerably better than first-year medical students, who, in turn, outperformed psychology students. Although the condition by expertise interaction was not significant, *F*(2,228)=0.8, *p* = .44, the magnitude of the effects of information structuring seem to vary systematically by expertise: Although only a negligible difference of structured information could be observed in the expert group (13.5 [SD = 4.5] vs. 13.0 [SD = 4.6], Cohen’s *d* = .11), we found a small effect size of information structuring in first-year medical students (9.9 [SD = 5.1] vs. 8.8 [SD = 4.5], Cohen’s *d* = .23), and a medium effect size in first-year psychology students (8.1 [SD = 4.3] vs. 5.7 [SD = 3.7], Cohen’s *d* = .60). In addition, as can be seen in Figure 2C, participants that viewed the InFARCt video provided higher ratings on items assessing comprehensibleness, structure, and willingness to recommend the physician to family and friends.

Overall, these results suggest that participants without expert medical knowledge (i.e., psychology students) can profit from information structuring during discharge communication events. The results are encouraging in suggesting that an intervention aimed at introducing information structuring in physicians’ communication can lead to improved recall of discharge information, perceived understanding, and increased satisfaction with the communication event.

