## Other Outcomes of Interest

Basic demographic measures concerning each patient as well as a number of other measures that will serve as covariates in the analysis, such as patients’ health status, memory ability, state anxiety, state depression, and medical knowledge. The rationale for including these measures is that they are potential moderators of participants’ recall of discharge information and thus should be included in the statistical analysis.

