## Assessments of outcomes

The pre-discharge assessment will take about 15 minutes and aims to collect basic demographic measures concerning each patient as well as a number of other measures that will serve as covariates in the analysis, such as patients’ health status, memory ability, state anxiety, state depression, and medical knowledge. The rationale for including these measures is that they are potential moderators of participants’ recall of discharge information and thus should be included in the statistical analysis.

Immediately after the discharge communication event, patients will be interviewed for up to five minutes to assess recall of information provided during the discharge consultation and to assess patients’ satisfaction with the encounter.

Finally, two brief interviews of 5–10 minutes will be conducted over the phone seven days after discharge and 30 days after discharge to retest recall of discharge information, thus assessing the reliability of the main outcome measure and the time component of recall. In addition, patients will be asked about self-reported adherence to discharge recommendations, and overall assessment of the discharge consultation. Table 5 provides a description of the measures collected in each phase. Patients will also be asked about information provided by their General Practitioners to control for possible confounds of receiving extra or additional information from a third-party.

Table 5. List of Measures Used in Patient Interviews and Respective Description

| Phase | Measure | Description |
| --- | --- | --- |
| Pre-discharge  Assessment | Demographics | Age, Sex, Education, Marital Status, Nationality |
|  | Health-related quality of life | German version of the SF-12,^29^ a generic, short-form health survey with 12 items developed to provide a valid and reliable method to monitor subjective aspects of health and quality of life. |
|  | Memory | CERAD Word List Memory test, a free recall memory  test that assesses learning ability for new verbal information.^30^ A ten-item word list is presented over three trials (at the rate of 1 every 2 seconds) with a different word order each trial. The participant is instructed to read each word aloud as it is presented and then asked to recall as many words as possible. |

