|  | State anxiety and depression | German version of the Hospital Anxiety and Depression Scale (HADS-D),^31^ a brief instrument containing two scales of 7 items assessing state anxiety and depression. |
|  | Medical knowledge | Multiple-choice test consisting of 6 questions of increasing difficulty developed by our research team. |
| Interview | Immediate recall | Patients will be asked to freely recall all information provided immediately after the discharge event, “Can you tell me all the information your physician just provided?”, and repeated use of prompts, “Was there any other information you can recall?” until the patient cannot recall any more information. |
|  | Satisfaction | Once patients cannot recall any additional information, they will be asked to characterize their satisfaction with the discharge communication event and physician. Specifically, we will previously developed items (see Study 4) asking patients to rate on a scale from 1 to 10 the (1) physician’s comprehensibleness, (2) information structuring, and (3) willingness to recommend the physician to family and friends. |
| Telephone Interview | Delayed recall | Patients will be asked to freely recall all information mentioned in the discharge event, “Can you tell me all the information your physician provided when you left the emergency department?”, and repeated use of prompts, “Was there any other information you can recall?” until the patient cannot recall any more information. In addition, patients will be asked whether they have received additional information from their general practitioner since discharge. |
|  | Adherence to recommendations | Patients will be asked to list all the physician recommendations that they have actively pursed, “Can you tell me which of your physician’s recommendations you have pursued?”. |
|  | Overall assessment | German version of the Patient Reactions Assessment (PRA-D),^32^ composed of three 5-item scales designed to measure information, affective, and communication components of physician–patient communication. |

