## Planned Analyses

The evaluation of the effects of the two training programs will be conducted using mixed-effects model.^33^ Mixed-effects models are statistical models containing both fixed (e.g., intervention program) and random (e.g., patient) effects and are used in a variety of disciplines including medical and social sciences, where repeated measurements are made on the same statistical units or on clusters of related statistical units. Specifically, our analysis will take into account the fact that physicians belong to particular clusters (see Study Design) and the same physician treats several patients, by clustering physicians by training program and patients by physician. These multivariate analysis methods also allow for simultaneous statistical adjustment for covariates of interest, including patient characteristics, such as age, memory ability, and so on. Similar models will be used to estimate the effect of the training programs on patient satisfaction, and adherence to discharge recommendations.

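### Section 5.2 puts satisfaction, rated after the intervention and itself a secondary outcome, into the analysis of recall; the training coefficient would then no longer estimate the total effect on recall

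*Protocol*

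**What the plan says.** Section 5.2 defines the secondary outcome as "Satisfaction with the discharge communication event and the physician directly after the discharge event". Its next sentence gives the reason for measuring it: "it is a potential moderator of participants’ recall of discharge information and thus should be included in the statistical analysis".

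Section 5.3 uses the same reason, in the plural, for health status, memory, state anxiety, state depression and medical knowledge. It describes these as "a number of other measures that will serve as covariates in the analysis". According to Table 5 they are collected before discharge.

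Elsewhere satisfaction is a result of training:

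- Section 4.3: "The secondary outcomes will be higher patient satisfaction".
- Section 11.4: "Similar models will be used to estimate the effect of the training programs on patient satisfaction, and adherence to discharge recommendations".

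Table 5 (section 9.2) fixes the order within the post-discharge interview: "Once patients cannot recall any additional information, they will be asked to characterize their satisfaction with the discharge communication event and physician". The three ratings cover comprehensibleness, information structuring and willingness to recommend the physician.

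On information from the family doctor, which is asked about at the telephone interviews, section 9.2 says: "Patients will also be asked about information provided by their General Practitioners to control for possible confounds".

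**The concern.** A covariate in a randomised comparison should be something that the intervention cannot have changed. Satisfaction does not qualify. It follows the training, the talk and the immediate recall task. One of its items asks about the behaviour being trained, so holding it constant comes close to holding delivery of the intervention constant. The team's own Study 4 reports that "participants that viewed the InFARCt video provided higher ratings on items assessing comprehensibleness, structure, and willingness to recommend" the physician.

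At stake is the meaning of the primary estimate. The primary objective (section 4.2) is recall as a function of training, which is a total effect. If satisfaction enters the recall model, the training coefficient compares patients who gave equal ratings after different training. That is a different quantity, and randomisation does not protect it. Reading *moderator* literally, as a training-by-satisfaction interaction, has the same flaw, because the subgroups would be formed by a response to the intervention.

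**Working it through.** **The protocol's own figures.** No figure is attached to the satisfaction sentence, so the check starts from the planning effects for recall. I assumed two-sided alpha .05 (the protocol states none) and independent patients (it gives no intracluster correlation). Power = Φ(d·√(n/2) − 1.96).

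- d = .59, n = 100 per condition (synopsis, over .9): Φ(4.17 − 1.96) = .987.
- d = .59, n = 50 (synopsis, above .8): Φ(2.95 − 1.96) = .839.
- d = .59, n = 75, i.e. 25% attrition (synopsis, above .9): Φ(3.61 − 1.96) = .951.
- d = .4, n = 100 per group, pairwise (section 11.2, .8): Φ(2.83 − 1.96) = .807.

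The stated powers reproduce when clustering is ignored. So .59 and .4 are fair reference values for the total effect.

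**Effect of adding satisfaction.** In SD units, let d be the training effect on recall, s the training effect on satisfaction (structuring minus emotion skills) and r the within-arm correlation of satisfaction with recall. Then

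adjusted effect = d − r·s.

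This is the algebra of covariate adjustment. It holds whether satisfaction acts on recall, recall acts on satisfaction, or both share a cause. A simulation with d = .59, s = .4, r = .3 gave .59 unadjusted and .47 adjusted, matching .59 − .3 × .4 = .47.

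**Inputs not in the protocol.** Study 4 gives a direction for the ratings but no size, and no document figure gives r. I assumed 0.2 to 0.4 for r and for the size of s, with s allowed either sign.

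- Smallest shift: 0.2 × 0.2 = 0.04 SD.
- Largest shift: 0.4 × 0.4 = 0.16 SD.

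| Total effect | Shift as % of total | Adjusted, s positive | Adjusted, s negative |
| --- | --- | --- | --- |
| .59 (synopsis) | 0.04/.59 = 7% to 0.16/.59 = 27% | .55 to .43 | .63 to .75 |
| .4 (section 11.2) | 0.04/.4 = 10% to 0.16/.4 = 40% | .36 to .24 | .44 to .56 |

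**One worked case for power.** Take d = .4, s = .4, r = .3 and 200 patients per arm, without clustering.

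- Unadjusted: Φ(.4 × √100 − 1.96) = Φ(2.04) = .979.
- Adjusted effect: .4 − .12 = .28. Residual SD: √(1 − .09) = .954. Variance inflation from the arm-satisfaction association: 1 + .16/4 = 1.04.
- Standard error: .954 × √(2/200) × √1.04 = .0973. Power: Φ(.28/.0973 − 1.96) = Φ(.92) = .82.

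The absolute powers are optimistic because patients share physicians and cohorts. The shift d − r·s does not come from that simplification.

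**The case against.** The strongest reply is that the protocol may not intend this adjustment. Section 5.2 speaks of a moderator and of inclusion in the analysis; it does not call satisfaction a covariate of recall. That reading comes from the matching sentence in 5.3. No covariate list names satisfaction, section 11.4 gives only patient characteristics as examples, and the same section models satisfaction as a dependent variable. The sentence may have been carried over from 5.3, and a statistical analysis plan may settle the list. All this stands, so a reader should not infer that the primary analysis is certain to be adjusted for satisfaction. But the sentence is current text, nothing confines it to exploratory work, and the examples in 11.4 are open-ended and do not override it.

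A reader might also infer that the adjustment necessarily removes part of the training effect. The documents do not support that. Study 4 compared structured with unstructured videos in students. The trial's control is an active training that section 3.6 credits with the potential to improve physician-patient interactions. If it raises satisfaction more, adjustment inflates the effect.

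Nor does a mediation account fit immediate recall, since the rating is taken after that recall is complete. It could apply at most to the 7- and 30-day recall.

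Information from the family doctor is a weaker matter. It is asked only by telephone, so it cannot touch immediate recall, and section 9.2 does not say how the control would be done. Table 1 includes advice to contact the family physician, so training could change it. Table 2, however, shows follow-up suggestions already present in 100% of recorded discharges, though of varying quality.

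**Conclusion.** The point holds in this form: section 5.2 assigns satisfaction a role in the recall analysis that its timing, its content and sections 4.3 and 11.4 rule out. If 5.2 is followed, the training coefficient no longer estimates the total effect on recall. That conclusion needs no number.

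The size is conditional. Under the assumed 0.2 to 0.4 for each unknown, the coefficient moves by 0.04 to 0.16 SD, which is 7-27% of .59 or 10-40% of .4. With a positive satisfaction-recall correlation, the move is towards zero if structuring raises satisfaction more than the control training does, and away from zero in the opposite case. The protocol fixes neither the sign nor the size.

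It is not established that the primary analysis will include satisfaction; 5.2 and 11.4 pull in different directions and must be reconciled before the recall model is settled. For family-doctor information the conclusion is limited to delayed recall: it too is collected after the intervention and should not drive the main estimate.

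**What to change.** 1. Delete the moderator sentence from section 5.2.
2. State in section 11.4 that covariates in the recall model are restricted to variables collected before discharge: for example age, education, CERAD memory, medical knowledge, SF-12, and the HADS-D anxiety and depression scores, since section 5.3 already names state anxiety and depression as covariates.
3. State that satisfaction is analysed only as an outcome of training, and that any analysis relating satisfaction to recall is exploratory.
4. For the 7- and 30-day recall, keep any adjustment for family-doctor information as a sensitivity analysis beside the unadjusted result.

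The cost is one deleted sentence and a few clarifying ones. Measures, visits, sample size and data collection stay as they are.
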